## Abstract

**Background:**

Post-transplant diabetes is a frequent and serious complication of kidney transplantation. There is currently no treatment to prevent or delay the disease. Nevertheless, identification of risk factors make it possible to target a population at risk of developing de novo diabetes. We hypothesized that a short-term treatment with vildagliptin may prevent new onset diabetes after transplantation (NODAT) in high-risk patients.

**Methods/design:**

This is a multicenter, double-blind, placebo-controlled randomized clinical trial. Patients undergoing first kidney transplantation will be included from ten French transplant centers. Included patients will be randomized (1:1) to receive either vildagliptin 100 or 50 mg/day (depending on glomerular filtration rate) during 2 months (the first dose being administered before entering the operating theatres) or placebo. Additional antidiabetic therapy could be administered according to glycemic control. The primary outcome is the proportion of diabetic patients 1 year after transplantation, defined as patients receiving a diabetic treatment, or having a fasting glucose above 7 mmol/l, and/or with an abnormal oral glucose tolerance test. Secondary outcomes include glycated hemoglobin, the occurrence of acute rejection, infection, graft loss and patient death at 3 months, 6 months, and 12 months after transplantation. Outcomes will be correlated to clinical and general characteristics of the patient, cardiovascular history, nephropathy, dialysis history, transplantation data, biological data, health-related quality of life, and the cost-effectiveness of prevention of diabetes with vildagliptin.

**Discussion:**

We have scarce data on the pharmacological prevention of post-transplant diabetes. If our hypothesis is verified, our results will have a direct application in clinical practice and could limit diabetes-associated morbidity, reduce cardiovascular complications, increase quality of life of renal transplant patients, and consequently promote graft and patient survival. Our results may possibly serve for non-transplant patients carrying a high-risk of diabetes associated with other co-morbidities.

**Trial registration:**

ClinicalTrials.gov, NCT02849899. Registered on 8 February 2016.

**Electronic supplementary material:**

The online version of this article (10.1186/s13063-019-3392-6) contains supplementary material, which is available to authorized users.

## Background

New onset diabetes after transplantation (NODAT) affects 15 to 20% of renal transplant patients and is associated with increased morbidity and reduced survival of both transplants and patients [1, 2]. Furthermore, our group identified NODAT as a risk factor for atherosclerotic events [3]. The majority of NODAT occurs in the first months following transplantation. Corticosteroids, anti-calcineurin, and mammalian target of rapamycin (mTOR) inhibitors have a major diabetogenic impact and greatly contribute to the increase in diabetes prevalence after transplantation. Some pre-transplant risk factors have been identified, offering the opportunity to define an individual risk of NODAT. Considering its impact on graft and patient survival, the ability to predict NODAT is a major issue. Chakkera et al. [4, 5] reported that a simple equation using six easily available parameters provided a good discrimination of risk and a good identification of high-risk populations for targeted prevention. The capacity to predict NODAT occurrence is the prerequisite to efficiently prevent or delay the onset of diabetes using appropriate therapeutic interventions.

To date, few studies have been performed on the pharmacological prevention of NODAT. Hecking et al. [6] recently reported that a short treatment with insulin, administered immediately after transplantation, reduced the incidence of de novo diabetes one-year post-transplant. The occurrence of diabetes, a secondary endpoint, was reduced by 73% in the treated group. However, NODAT was a secondary endpoint and the side effects of insulin are not necessarily compatible with a preventive strategy. Relevant experimental evidence suggests that gliptins could be used in the pharmacological prevention of NODAT. Indeed, beyond the effects on blood glucose, gliptins have other actions, including a protective effect on β cells and anti-inflammatory action that could prevent or delay the occurrence of new-onset diabetes after renal transplantation in patients at risk [7–10]. The gliptins are approved for the treatment of type 2 diabetes, among which vildagliptin was used to treat diabetes after kidney transplantation in two clinical studies [11, 12]. These studies showed the anti-diabetic effect of vildagliptin taken early in the disease, but not as a preventive treatment for diabetes. Our hypothesis is that a short-term treatment of vildagliptin administered in the early post-transplant period may prevent the occurrence of NODAT.

## Methods/design

### Study design

This is a multicenter, double-blind, placebo-controlled randomized clinical trial. The study will include 186 patients receiving a kidney transplant and matching the criteria for inclusion. Recruitment will be done in ten French transplant units: Amiens, Besançon, Brest, Lille, Nice, Paris (Necker and Tenon), Rennes, Poitiers, and Tours. Patients will be randomized into two groups: group 1 will be treated with vildagliptin and group 2 will be treated with placebo. The treatment duration will be 2 months. The dose will be adjusted during treatment, depending on the results of glomerular filtration rate. The administration of vildagliptin begins before entering the operating theatre. Blood glucose is controlled and if necessary hyperglycemia will be treated according to current recommendations, regardless of the group and the study.

### Participants

#### Inclusion criteria

Graft recipients aged 18 or above will be eligible for inclusion if they:Receive a first kidney transplantAre considered at high risk of developing NODAT, having at least two of the three following criteria: age > 50 years; body mass index (BMI) > 30 kg/m^2^; direct family history of type 2 diabetesCan receive immunosuppressive therapy including tacrolimus, mycophenolic acid, and steroidsAre patients in whom the cessation of steroids may be considered at the latest 3 months post-transplantSign the informed consent for study participationAre affiliated with a medical care system

#### Non-inclusion criteria

Graft recipients will not be eligible for inclusion if they have the following conditions:Legal disability or limited legal capacityPatient unlikely to cooperate in the study and/or low early cooperation by the investigatorPatient without health insurancePregnancy and breast feedingHepatic insufficiencyPatient with class IV New York Heart Association (NYHA) heart failurePatient with galactose intolerance, Lapp lactase deficiency, or glucose-galactose malabsorption syndromePatient in the period of exclusion of another study or under the “National Register of Volunteers”Inability to understand the reasons for the study; psychiatric disorders judged by the investigator to be incompatible with the inclusion in the studyActive infectionInfection with hepatitis C virusA history of diabetesA history of pancreatitisA history of angioedemaMulti-organ transplantation

#### Participant recruitment

The study will be proposed to patients receiving a kidney transplant and matching the criteria of inclusion. The information sheet is given after admission for kidney transplant. The history of diabetes is checked during the inclusion consultation and in the medical file. Then the physician collects informed consent before going to the operating theatre. Recruitment will be done in ten French transplant units (Amiens, Besançon, Brest, Lille, Nice, Paris (Necker and Tenon), Rennes, Poitiers, and Tours). Delay may be shorter than the recommended time, but it corresponds to the studies on transplantation for which only a few hours are available between patient admission and surgery. Then, patients will be randomized.

#### Randomization

Patients will be randomized 1:1 into two groups using a minimization technique with stratification according to center and the number of risk factors for developing diabetes (two or three).Group 1 (interventional group) will be treated with vildagliptin 100 or 50 mg/day for 2 months (depending on whether their glomerular filtration rate is above or below 50 ml/min; Modification of Diet in Renal Disease (MDRD) equation).Group 2 (placebo group) will be treated with placebo according to the same dosage.

Random allocation sequence is generated using CleanWeb™. The minimization algorithm takes into account already randomized patients in order to allocate a new treatment to minimize difference between stratification criteria. The randomization result provided by the system is attributed in 80% of cases; otherwise, the other treatment is attributed. Neither the nurse nor the doctor nor the patient will know the nature of the ingested tablets. The blinding is created by the clinical research associate coordinator. The randomization number is assigned directly to the centers via CleanWeb™.

### Interventions

#### Timing of administration of the study treatment

First administration of the study treatment (vildagliptin or placebo) will be performed within hours prior to patient departure to the operating room. The dosage of vildagliptin will conform to the marketing authorization of data in its indication in the treatment of diabetes in kidney transplant patients. Patients will receive a half dose of therapy until they have a glomerular filtration rate greater than 50 ml/min of (MDRD equation). Patients will receive one oral tablet in the morning and one in the evening (100 mg per day) or just one in the morning (50 mg per day) for 2 months.

#### Posology change

The glomerular filtration rate will be measured each week and treatment changed accordingly. Blood glucose will be controlled and, if necessary, hyperglycemia will be treated according to current recommendations, regardless of the group and the study.

#### Premature discontinuation of the study treatment

All suspected adverse reactions related to the investigational medicinal product which occur during the present trial and that are both unexpected and serious are subject to expedited reporting. Based on the risk management plan for vildagliptin, subsequent adverse events will be followed attentively and considered as adverse events of special interest, including gastrointestinal disorders, pancreatitis, hepatitis, skin reaction, infection, neurotoxicity, pancreatic cancer, and cardiac disorders. These reactions will be recorded in the electronic case report form (e-CRF) and transmitted to the sponsor in cases of serious adverse events. In this case, the investigator reserves the right to prematurely terminate the study treatment for medical reasons. The reasons for premature discontinuation should be properly documented.

#### Appropriate administration of treatment units

A record of the number of tablets dispensed to and taken by each subject must be maintained and registered in the CRF. Compliance with therapy will be assessed through querying the patient during visits and examination of pillboxes given back at the endpoint.

#### Unblinding modalities

If serious adverse events attributable to the study product occur, a blind lift procedure may optionally be initiated both by investigators and by the pharmacovigilance unit of the University Hospital. In the latter case, the unblinding will be carried out by the data manager on request of the head of pharmacovigilance. Clinicians as well as biostatisticians retain the blind.

#### Concomitant medication

Vildagliptin is an approved treatment for NODAT in patients with renal failure. It will be used in these patients as a preventive treatment according to the same recommendations as in curative treatment. Vildagliptin has a low potential for drug interactions. It is neither a substrate nor an inhibitor or inducer of cytochrome P450 (CYP450) enzymes; therefore, it is unlikely to interact with active substances that are substrates, inhibitors, or inducers of these enzymes. Clinical studies showed no pharmacokinetic interactions clinically relevant to vildagliptin with other antidiabetic treatments (pioglitazone, metformin and glibenclamide, digoxin, warfarin, amlodipine, ramipril, valsartan, or simvastatin). Therefore, no treatment (antidiabetic or not) is prohibited because of the study. As with other oral antidiabetic agents, the hypoglycemic effect of vildagliptin may be reduced by certain active substances, including thiazides, corticosteroids, thyroid hormones, and sympathomimetics. As in conventional treatment, however, these treatments are not prohibited. In conclusion, the prescription of vildagliptin for this study does not modify medical care of included patients (whether for immunosuppressive treatment or for antidiabetic treatments).

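### The rule that no antidiabetic is prohibited makes no exception for open-label vildagliptin or other DPP-4 inhibitors during the two blinded months

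*Protocol article*

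**What the plan says.** The Concomitant medication section opens with "Vildagliptin is an approved treatment for NODAT in patients with renal failure". It then reports "no pharmacokinetic interactions clinically relevant to vildagliptin with other antidiabetic treatments (pioglitazone, metformin and glibenclamide" and several drugs that are not antidiabetics, and concludes: "Therefore, no treatment (antidiabetic or not) is prohibited because of the study". It closes by saying that "the prescription of vildagliptin for this study does not modify medical care of included patients (whether for immunosuppressive treatment or for antidiabetic treatments").

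Rescue is described in the same open way in the Abstract, Study design, Posology change and Study visits: high blood glucose is treated as glycemic control or current guidance requires, and no class is named or excluded.

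Three other sections matter here:

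- **Dose.** Timing of administration of the study treatment says "The dosage of vildagliptin will conform to the marketing authorization" and "Patients will receive a half dose of therapy until they have a glomerular filtration rate greater than 50 ml/min". That means 50 mg/day, then 100 mg/day, for 2 months.
- **Blinding.** Randomization says "Neither the nurse nor the doctor nor the patient will know the nature of the ingested tablets".
- **Unblinding.** Unblinding modalities says "If serious adverse events attributable to the study product occur, a blind lift procedure may optionally be initiated".

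**The concern.** The permission is universal and names antidiabetics. It is a rule that the article states, not a detail left to another document. Its reasoning is narrower than its conclusion: interaction data with pioglitazone, metformin or glibenclamide cannot support adding vildagliptin to vildagliptin, or another DPP-4 inhibitor to it.

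The article also makes vildagliptin an eligible rescue drug. It calls it approved for NODAT in renal failure, and the Discussion prefers it to sitagliptin partly because of renal impairment. The Background says that most NODAT arises in the first months, which overlap the blinded period.

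Two things are at stake. A patient on active study drug could exceed the dose that the protocol sets by GFR. A placebo patient could receive the tested intervention during the tested window. The prescriber could not know which of the two was happening.

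**Working it through.** **1. Is there an exception anywhere?** The sections that bear on rescue, read side by side:

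| Section | What it allows or limits |
|---|---|
| Concomitant medication | Everything allowed, antidiabetics included |
| Abstract, Study design, Posology change, Study visits | Rescue as needed, class left open |
| Timing of administration | GFR-based dose, written for the study treatment |
| Posology change | Weekly GFR check, adjusts the study treatment only |
| Randomization | Nurse, doctor and patient blinded to the tablets |
| Unblinding modalities | Route for serious adverse events attributed to the product, not for choosing a rescue drug |

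None of these excludes the study drug or its class as rescue. They do not contradict each other; one exception is missing from a blanket rule.

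**2. Dose if a full labelled dose of open-label vildagliptin is added in the active arm.**

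- GFR below 50 ml/min: 50 + 50 = 100 mg/day, against 50 planned (ratio 2).
- GFR above 50 ml/min: 100 + 100 = 200 mg/day, against 100 planned (ratio 2).

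For another DPP-4 inhibitor the issue is duplication of the class, not a doubled vildagliptin dose.

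**3. The plan's own sample size.** Inputs from Sample size and power calculation: 40% against 20%, two-sided 5%, 80% power. For a fixed design with pooled variance:

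n = [1.960·√(2·0.30·0.70) + 0.842·√(0.40·0.60 + 0.20·0.80)]² / 0.20² = 81.2, so 82 per arm.

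The stated 84 fits this with one interim look. At 84 per arm and the final level of 0.049, power is 81.1%.

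**4. Which way would crossover move the 1-year difference?** The article gives no rescue rate, stopping rate or rescue benefit, so these cases are assumptions. Let c be the share of placebo patients given an open-label gliptin, at average 40% risk. The vildagliptin rate stays at 20%.

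| Assumed case | Placebo rate | Difference at c = 10/20/30% | Power |
|---|---|---|---|
| All stop before M12, full planned benefit | 0.40 − 0.20c | 18/16/14 points | 73/64/53% |
| All still treated at M12, so counted diabetic under Study outcomes | 0.40(1 − c) + c | 26/32/38 points | 95% to over 99% |
| No lasting effect, stopped before M12 | 0.40 | 20 points | 81% |

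The first two effects cancel when a share s of the crossovers is still treated and the rest get the full benefit: s + (1 − s)·0.20 = 0.40, so s = 0.25.

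**5. Would the exception recover power?** Insulin stays allowed. The Discussion cites a 73% reduction in diabetes with early insulin. If that applied to rescued placebo patients who stop before M12, the placebo rate would be 0.40(1 − 0.73c), and power 69/54/38% at c = 10/20/30%. This is lower than in the corresponding gliptin case. Steps 4 and 5 ignore rescue in the vildagliptin arm and the interim look. Rescue would also select higher-risk patients, so no row is a bound.

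**The case against.** The best reply is that the section concerns what may accompany vildagliptin, so the sentence means that no *other* agent is barred. It also says only that the study adds no prohibition; ordinary prescribing limits and the marketing authorization still apply. Staff know that the trial drug is vildagliptin and can choose another class. Usual-care rescue is a legitimate pragmatic choice. The full protocol, which is not shown, may contain rescue guidance.

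Much of this is fair. The charitable reading is plausible, and a careful prescriber may avoid the class unprompted. But the sentence does not say so, and the dosage clause is written for the study treatment. Ten centers should not have to infer the exception. Because the article states a positive rule, pointing to the full document does not cure it.

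A reader might infer more than the article supports:

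- *That the trial loses power, or that the fix restores it.* The direction is unknown, and the comparison with no crossover is the wrong one for judging the fix. With gliptins excluded, the same patients would be rescued with insulin or another class, and would still count as diabetic if treated at M12.
- *That duplicate use will be common.* Nothing in the article suggests this.
- *That the doubled dose is shown to be harmful.* The article gives no evidence on 100 mg/day at low GFR or on 200 mg/day.
- *That the protocol contradicts itself.* It does not.

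**Conclusion.** The point holds as a cheap improvement, on two grounds only: possible duplicate dosing in the active arm, and possible exposure of placebo patients to the experimental drug between D0 and M2. The dose would double (50 to 100, or 100 to 200 mg/day), assuming that a full labelled dose of vildagliptin is added. The frequency is not given. The effect on the 1-year difference is unknown in size and sign: it narrows mainly if rescue works and is stopped before M12, and it can widen if rescue continues. The power figures only illustrate this and carry no weight in the conclusion. Under the blind, and without an unblinding route for this purpose, the workable safeguard is not to use the class.

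**What to change.** Add one sentence to Concomitant medication: from D0 to M2, open-label vildagliptin and other DPP-4 inhibitors are not to be used as rescue; insulin and all other classes are unrestricted. Add that, if such use occurs, the patient stays in the ITT analysis and the use is logged as a protocol deviation.

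The cost is a protocol amendment and a small, temporary limit on the choice of rescue class. Logging needs little new data, since Health economics analysis already counts diabetes treatment from D0 to M12. Trial status reports seven patients enrolled at submission, so on that count an early amendment would have covered nearly all of the planned 186.

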### Study outcomes

The primary endpoint is the proportion of diabetic patients 1 year after transplantation, defined as one of the following criteria: patients receiving a diabetic treatment, patients have a fasting glucose above 7 mmol/l, and/or patients with an abnormal oral glucose tolerance test (OGTT).

The criteria for secondary assessments are: glycated hemoglobin (HbA1c) 3 months, 6 months, and 12 months after transplantation; occurrences of acute rejection, infection, graft loss, and patient death 3, 6, and 12 months after transplantation; clinical history (cardiovascular history, baseline renal disease, dialysis, anti-human leukocyte antigen antibodies, dyslipidemia, hypertension, type of donor, duration of ischemia, cytomegalovirus (CMV) status, CMV prophylaxis, pneumocystis prophylaxis); biological data (creatinine, uric acid, C reactive protein (CRP), blood sugar balance, lipid profile, liver function tests, pancreatic balance, and blood counts); health-related quality of life (HRQoL; Renal Transplant Quality of Life (ReTransQoL) questionnaire), 8 days and 3, 6, and 12 months after transplantation; and the cost-effectiveness of prevention of diabetes with vildagliptin correlated to outcomes.

### Study visits

As presented in Fig. 1 (Additional file 1), the study will include five visits (D0, D8, M3, M6, and M12) corresponding to those taking place in the context of the current follow-up after a kidney transplant. During these visits, clinical examination and a blood test will be conducted as part of the study to collect necessary clinical data in each center on case report forms and to determine the different dosages in the hospital laboratories, respectively. Blood glucose will be controlled and, if necessary, hyperglycemia will be treated according to current recommendations, regardless of the group and the study. The HRQoL will be estimated using the ReTransQoL questionnaire and the health-utility with the EQ-5D questionnaire (EuroQol questionnaire with five dimensions). The benefits of prevention of NODAT will be evaluated by estimating the cost of patient care during the first year of transplantation (care, medicines, medical examinations, hospitalization, etc.).

**Fig. 1 Fig1:**
[figure not shown]
SPIRIT figure of the PRODIG study

### Adverse effects

The risks associated with participation in the study are those related to an additional blood sample, either hematoma, redness, vagal malaise, and those related to the glucose tolerance test, including nausea, vomiting, malaise, sweating, tremors, palpitations, hunger, and confusion. The risks associated with taking vildagliptin are those described for its use as an antidiabetic treatment (vildagliptin ((S)-1-[N-(3-hydroxy-1-adamantyl)glycyl]pyrrolidin-2-carbonitrile; N° Chemical Abstracts Service, 274901165). Based on the risk management plan for vildagliptin, adverse events will be following attentively and considered as adverse events of special interest, including gastrointestinal disorders, pancreatitis, hepatitis, skin reaction, infection, neurotoxicity, pancreatic cancer, and cardiac disorders. Particular attention will be given to adverse events occurring at the national level, including hepatitis, pancreatitis, rash, infections, pancreatic cancer, bullous eruption, and cardiovascular serious adverse events. In addition, when combined, inhibitors of angiotensin converting enzyme and antagonists of angiotensin II receptor (ARA2) will be used with caution.

